## Abstract

**Introduction:**

Men with prostate cancer undergoing treatment commonly report poorer cognitive performance than their age-matched controls. Within other populations, modifiable risks factors including cognitive and physical activity can independently provide potent cognitive and neuroprotective benefits. However, greater benefits may be achieved by combining stimuli simultaneously (concurrently) to promote greater neurogenesis, connectivity, and improved cognitive outcomes. This approach has been tested in older populations with and without cognitive impairment, but initial acceptability, feasibility and efficacy are yet to be demonstrated in men affected by prostate cancer. This research aims to (1) demonstrate the acceptability and feasibility of a concurrent cognitive and physical training intervention against pre-set progression criteria and, (2) provide initial estimates of intervention effectiveness on cognitive function, fatigue, and quality of life in men with prostate cancer on ADT.

**Methods:**

Seventy-six men diagnosed with prostate cancer receiving androgen deprivation therapy will be the recruitment target. This pilot and feasibility study will employ a randomized controlled trial design where participants will be assigned to one of four groups: (1) concurrent training—moderate intensity stationary cycling whilst simultaneously performing computerized cognitive training, (2) moderate intensity stationary cycling only, (3) computerized cognitive training only or (4) wait-list control group. Training will be completed twice a week for 8 weeks, building up to 60 min per session. Assessment of the first aim will include an appraisal of recruitment success, adherence, adverse events, subjective acceptability, and the principle of no cognitive harm in response to the intervention. In line with aim two, additional measures will include a computerized cognitive battery and subjective questionnaires on cognition, fatigue, and quality of life.

**Discussion:**

Internationally, many men continue to grapple with the debilitating effects of cognitive decline after a diagnosis and associated treatment with little, or no, evidence-based self-management strategies advised in practice. This timely research will explore the feasibility of concurrent training to treat the cognitive side-effects of androgen deprivation therapy and, in turn, inform the design of a future large-scale clinical trial.

**Clinical trial registration:**

https://anzctr.org.au/Trial/Registration/TrialReview.aspx?id=385591&isReview=true, identifier ACTRN12623000767606.

## Background

1

Globally, prostate cancer is the second most common cancer among men (1) with rising incidence rates concomitant with an ageing population and improved screening (2, 3). Although the prognosis is favorable in most high-income countries, and the associated mortality rates have continued to fall since the mid 1990’s (4), many men continue to experience severe side-effects from the cancer and associated treatments with little or no self-management advice (5). Specifically, Androgen Deprivation Therapy (ADT) is commonly associated with distressing levels of fatigue (6), coupled with a higher predisposition to cardiovascular disease, diabetes and depression (5, 7). Side-effects such as fatigue have successfully been the target of several intervention strategies including pharmacological aid and varying forms of physical activity (8, 9).

Compared to other side-effects, cognitive disruptions related to prostate cancer and it’s treatment have received less attention in research, but include both objectively assessed deficits and subjective complaints (10, 11). The exact cause of these cognitive disruptions remain unclear, although ADT is often implicated (10). For instance, ADT has been linked to structural (12, 13) and functional changes in the brain (12). In addition, executive functioning has been shown to be impacted by ADT (14, 15) as well as verbal memory (14, 16, 17) attention (14, 16), processing speed (16), visual processing (18) and spatial ability (18). Indeed, there is evidence that the discontinuation of hormone therapy in men with prostate cancer is associated with better cognitive ability for verbal memory tasks (19). Regardless of the specific cause of cognitive side-effects related to prostate cancer treatments, preventing and mitigating these side-effects requires more attention. Given the likely link between structural and functional brain pathways, as well as a higher level of cognition potentially mitigating excessive cognitive fatigue day to day, interventions that can promote improvement in these areas, like engaging in physical and cognitive activity, are well positioned to support men with prostate cancer in the future.

There is good evidence to support the benefits of physical activity on cognitive function across the lifespan (20, 21), but related research in cancer is largely limited to breast cancer (22, 23). In prostate cancer, the limited evidence suggests that men who report greater levels of physical activity perform better on assessments of memory, attention and executive function (24). Within intervention studies, a scarcity of evidence exists, although 8-weeks of combined aerobic and resistance exercise was found to be associated with improvements in self-reported cognitive function (25). This initial evidence, while limited, aligns with findings in other populations and supports the potential for physical activity to benefit cognitive function in men with prostate cancer. As such, there is a clinical need for physical activity-based intervention studies with objective measures of cognitive function to inform the relative effectiveness of interventions for cognition in this high-risk population.

Another intuitive avenue to target cognitive function is through cognitive training, with recent meta-analytical evidence (26) supporting its use to improve cognitive function in older adults without cancer. An initial pilot study in men with prostate cancer receiving ADT suggests that a computerized cognitive training intervention for 1 h/day, 5 days/week for 8 weeks can improve reaction time in this population (27). Given the rigorous nature of this intervention, further research is required to determine whether a less intensive and time-consuming intervention that incorporates standard care physical activity recommendations may provide as good or greater benefits to cognition and mitigate cognitive fatigue.

Given the evidence for both cognitive and physical training approaches to benefit cognition, there is understandable clinical interest in whether these interventions can provide additive benefits when delivered in a time efficient, simultaneous (concurrent) manner in this population. Such an approach may not only provide added benefits but ease the time burden on self-management behaviours, addressing wellness and quality of life.

Recent meta-analytical evidence highlights that cognitive training, performed concurrently with physical training, can provide superior cognitive benefits for older adults with and without cognitive impairment when compared to other lifestyle interventions alone (28, 29). Concurrent interventions that include cognitive and physical training completed simultaneously are proposed to deliver superior neurogenesis (30) and neuroplasticity (31) in the brain, and improved cognitive outcomes (32) compared to the delivery of these treatments in isolation. Emerging clinical evidence further supports this multimodal approach, demonstrating that combining aerobic exercise with cognitive training leads to meaningful improvements in cognitive performance and broader clinical outcomes, reinforcing its potential as an effective non-pharmacological strategy to mitigate cognitive decline (33). These benefits could extend to improvements in cancer-related fatigue, providing low-cost, time-efficient opportunities for men with prostate cancer to reduce potential side-effects of the cancer and its treatments. It is unclear however, whether the two interventions can be delivered together and tolerated in this clinical population given the concerns around cancer-related fatigue. Consequently, a key initial step prior to more detailed investigations is to assess the acceptability and feasibility of an intervention that involves concurrent cognitive and physical training (i.e., cycling while completing computerized cognitive tasks) in this population.

Thus, the current study is designed to investigate the acceptability and effectiveness of concurrent cognitive and physical training to alleviate potential cognitive side-effects for men with prostate cancer receiving ADT. The design of this pilot study addresses the following aims (1) investigate the acceptability and feasibility of a concurrent cognitive and physical training intervention in men with prostate cancer against preset progression criteria and (2) provide initial estimates for the effect of a concurrent cognitive and physical training intervention on cognitive function, fatigue and quality of life outcomes in this population. We hypothesize that (1) concurrent cognitive and physical training will be an acceptable and feasible intervention among men diagnosed with prostate cancer receiving ADT and that (2) the concurrent cognitive and physical training intervention will provide positive cognitive, fatigue and quality of life benefits compared to training those modalities in isolation and the wait-list control group.

## Methods

2

This research will be conducted in the Australia Capital Territory (Australia) at the University of Canberra Cancer Wellness Centre. The intervention will be delivered by a team of Accredited Exercise Physiologists who will supervise all intervention sessions.

### Study design

2.1

The proposed study protocol is an 8-week pilot randomized controlled trial (Figure 1), which will be conducted and reported according to the Consolidated Standards of Reporting Trials (CONSORT) and Standard Protocol Items: Recommendations for Interventional Trials (SPIRIT) guidelines (Figure 2) (34), for pilot and feasibility trials. The CONSORT (Additional File 1) and SPIRIT checklists (Additional File 2) are presented in the Supplementary material.

**Figure 1 fig1:**
[figure not shown]
Overview of study design.

**Figure 2 fig2:**
[figure not shown]
SPIRIT Figure. *Feasibility measures including adverse events and adherence will be monitored throughout the intervention period. Recruitment success will be monitored on a 6 monthly basis and subjective acceptability of the study will be captured at the end of the 8-week intervention for each participant via an exit survey.

The experimental protocol will consist of (1) eligibility screening and informed consent, (2) baseline cognitive health, fatigue, quality of life and physical activity questionnaires, (3) pre-intervention objective cognitive and physical assessments, (4) 8-week training intervention with mid-point questionnaires and (5) post-intervention questionnaires and objective testing, as per Figure 2.

This study has been approved by the University of Canberra Human Research Ethics Committee (#11955). Any amendments to the protocol will be approved by the University of Canberra Human Research Ethics Committee and subsequently submitted to the Australia and New Zealand Clinical Trial registry ACTRN12623000767606 and the funder.

### Participants

2.2

The recruitment target is 76 men with prostate cancer over an ~18-month period. Participants will be recruited from the Australian Capital Territory (ACT) and surrounds utilizing the multidisciplinary team’s professional and clinical networks including public and private hospitals. The research team is highly connected to potential recruitment groups. The team includes a Medical Oncologist at The Canberra Hospital and the President of the ACT Prostate Cancer Support Group. The ICON Cancer Centre (co-located with the University of Canberra) will further support recruitment strategies. Outside of these direct routes of participant recruitment, the study will be advertised with flyers in cancer-related clinics, aged care settings and via traditional and social media outlets.

The annual incidence of prostate cancer in the ACT is approximately 260 new cases (35). The recruitment target requires a participation rate of 19.5% of the approximate 390 cases expected in the 18 months the study will be recruiting within.

Eligible participants must meet the following inclusion criteria:

Male >18 years old, diagnosed with prostate cancer currently receiving primary ADT for either metastatic or nonmetastatic hormone-sensitive prostate cancer.Received at least one dose of ADT within the last 6 months.Self-assessed reading and writing English proficiency.Able to provide written informed consent and expected life expectancy of more than 12 months.

Although eligibility is open to men aged ≥18 years to maximize inclusivity, the study population is expected to consist predominantly of older adults, as prostate cancer incidence and the use of androgen deprivation therapy are highest in this age group.

Based on known interactions with the primary outcome measures, participants will be excluded if (1) they have received chemotherapy or radiation within the last 3 months; (2) they are treated with steroids equivalent to more than 10 mg of prednisolone a day; (3) they have consumed opioid-based analgesics within the last 28 days; (4) they have a history of neurological injury/illness; or (5) they suffer from a concomitant major psychological illness (i.e., bipolar disorder or psychosis).

Participants must be able to complete all aspects of the physical and cognitive intervention. An Adult Pre-Exercise screening will be conducted over the phone in the screening process to confirm eligibility which is verified in an initial baseline familiarization visit. During this visit, a member of the research team (an Accredited Exercise Physiologist) will confirm eligibility as discussed on the phone in advance, and outline the study procedures, as per the participant information form. The participant is then provided with an opportunity to ask any questions in relation to the study. Participants will be reminded that engagement in the study is completely voluntary, and that they have the right to withdraw at any time, without reason.

If the eligible participant is happy to proceed, they will then be asked to read and sign a consent form (Additional File 3), which will be witnessed and signed by a member of the research team. Following this, the participant will then complete all pre-intervention questionnaires related to demographic health including education level and alcohol intake (Alcohol Use Disorders Identification Tool), as well as subjective cognitive function, fatigue, quality of life (detailed below) and physical activity behaviors (International Physical Activity Questionnaire). Participants are invited to complete these questionnaires on a computer or pen and paper, based on participant preference. Finally, the participant is invited to complete a short familiarization of the objective computerized cognitive function assessments as an additional screen to confirm sufficient computer literacy. Once complete, participants will attend the laboratory on a separate occasion to complete the full objective cognitive and physical pre-intervention outcome assessments also detailed below.

### Randomization, group allocation, and blinding

2.3

All participants who give consent and fulfill the inclusion criteria will be stratified by age (+/− 65 years) and then randomly allocated in a 1:1:1:1 ratio to one of four treatment arms: (1) physical training, (2) cognitive training, (3) concurrent cognitive and physical training, or, (4) wait-list control. Randomization will use a computer-generated sequence of numbers in blocks of variable sizes in a 1:1:1:1 ratio by a researcher not directly involved in the study. Allocation concealment will be ensured using sequentially numbered, opaque, sealed envelopes prepared by this independent researcher and kept inaccessible to recruitment and assessment staff until completion of baseline testing. After baseline testing (outlined below), this envelope with the group allocation will be delivered to the participant and training staff. Once opened, the training staff will provide information to the participant about the allocated intervention arm. Blinding of intervention allocation is not possible for any participant or the training staff. Team members completing the post-intervention assessments will be blinded to participant group allocation and will not be involved in data analysis. Treating clinicians involved in referring potential participants to the study (including author GP) will be blinded to whether potential participants choose to engage with the study.

### Sample size and power calculation

2.4

Determining sample sizes in pilot studies typically uses various methods to select samples that are representative of the population of interest. These methods have included less stringent justifications, often applying concepts related to a ‘rule of thumb.’ Sample size must ultimately provide sufficient representation of the population to assess feasibility and acceptability. However, it should also provide initial effect estimates to inform progression to larger trials. In line with recommendations for efficient and timely pilot studies (36), we have undertaken a modified power analysis utilizing an adjusted alpha (*α* = 0.25). This approach prioritizes the identification of preliminary effect signals that may warrant further investigation in a fully powered trial, while recognizing that any findings at this stage are exploratory and will be interpreted with appropriate caution.

As a result, we propose to recruit 77 participants, which will result in 19 per intervention arm in a 1:1:1:1 ratio. To inform this initial power analysis, we utilized a meta-analysis (28), comparing concurrent training to physical training in older adults. This power analysis was based on a four-arm study, with an effect size of *d* = 0.24, 80% power with *α* = 0.25.

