Benefit likelihood	If results suggest likely harm across most cognitive outcomes (e.g., Consistent negative effect sizes)	Results suggest potential harm. Consider changes to protocol.	Results are neutral or positive in effect size across most cognitive outcomes. Proceed to larger trial.

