#### Cognitive function

2.6.7

The benefit likelihood on cognitive function will be assessed pre- and post-intervention in a single sitting, with participants located individually in a quiet room with minimal distractions. Potential harm will be defined as negative effect sizes consistently across most cognitive outcomes, clearly favoring the control group. Participants will be seated with a laptop and mouse at an individual desk and will be instructed to perform the tasks as quickly and accurately as possible. All tasks were downloaded on 6th April 2022 from the Millisecond (Seattle, USA) test library using the Inquisit Player version 6.5.2 and will be delivered in English (42). Some modifications to the base scripts will be made to be more suitable for this population including changes in timings, trial number, and colloquial understandings. Each assessment will include a series of practice trials to be completed before test trials. The cognitive battery takes ~50 min to complete and consists of five tasks in the cognitive domains that have been reported to potentially be impacted by ADT including visuospatial skills, spatial memory, and executive functioning (10). Such domains may also be responsive to concurrent training (28). Category Switch will be the first assessment and will assess executive function through a divided attention task (43). This will be followed by the Visual Simon task assessing executive function, working memory and inhibition (44). The next assessment will be the Groton Maze test assessing immediate and short-term visuospatial memory (45). The second last assessment will be the Visual Search task (Divided Attention) which is a divided attention task assessing visuospatial skills and spatial memory (46). Lastly, the Psychomotor Vigilance test assesses attention, response speed and motor co-ordination (47).

Visuospatial awareness (and fine motor skills) will also be assessed with the Purdue Pegboard. It involves the participant placing as many small pegs as possible into a pegboard in 30 s, with both their dominant hand, non-dominant hand, as well as both hands simultaneously. This assessment has specifically been included as visuomotor slowing has been shown in those with advanced prostate cancer (McGinty et al., 2014; Salminen et al., 2004) and may be sensitive to physical activity.

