### Statistical analysis

2.7

Quantitative analyses will be conducted in the R statistical package. Analyses will follow an intention-to-treat principle, whereby all randomized participants will be included in the groups to which they were allocated, regardless of adherence or withdrawal. The mean and standard deviation of the outcome measures pre-, mid-, and post-intervention will be calculated for each group. Group differences in baseline characteristics will be assessed with one-way ANOVA or Kruskal-Wallis test (pending normality of data). Data related to the feasibility of the intervention (e.g., adherence and adverse advents) will be reported as frequencies. To estimate intervention effects (i.e., cognitive and fatigue outcomes), Linear Mixed Models with a random intercept fitted for subjects will be implemented using the lme4 package (60), to consider the repeated measures nature of the data and interindividual variability. These models inherently accommodate incomplete outcome data under a missing-at-random assumption. As per previous work (22), hypothesis testing from pilot studies should be interpreted with caution, as the small sample sizes can result in imprecise estimates and are unlikely to reach statistical significance. Effect sizes will be calculated for the pairwise changes in primary outcome measures between the experimental conditions. Effect sizes will be calculated as Cohen’s d using the pooled standard deviation of the random effects to account for a Linear Mixed Model structure. Effect sizes will be interpreted as small, moderate, and large based on cut-off points of 0.2, 0.5 and 0.8, respectively.

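### The α = 0.25 and 80% power in section 2.4 do not describe the progression rule, and 80% does not hold for concurrent versus physical training at 19 per arm

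*Protocol article*

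**What the plan says.** **Sizing (section 2.4).** The text reports that "we have undertaken a modified power analysis utilizing an adjusted alpha" of 0.25, presented as a way to find early signals worth pursuing in a fully powered trial, with findings labelled exploratory. The effect size is taken from a meta-analysis "comparing concurrent training to physical training in older adults". The inputs are given in one sentence: "This power analysis was based on a four-arm study, with an effect size of *d* = 0.24, 80% power with *α* = 0.25". The result is 19 per arm. Neither the test nor its sidedness is stated.

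**Progression (section 2.6.2, Table 1).** The go column of the Benefit likelihood row reads: "Results are neutral or positive in effect size across most cognitive outcomes. Proceed to larger trial". The row names no α, interval or comparator. Section 2.6.7 adds: "Potential harm will be defined as negative effect sizes consistently across most cognitive outcomes, clearly favoring the control group". The row is one of five criteria; mixed findings are to be read together, with safety and acceptability given priority.

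**Analysis (section 2.7).** Linear mixed models are planned, with Cohen's d for pairwise changes between conditions. No α is named. A general caution on testing in pilot studies says that "the small sample sizes can result in imprecise estimates and are unlikely to reach statistical significance".

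**Hypothesis 2 (end of Background).** Concurrent training is expected to do better than each modality alone and better than the wait-list.

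**The concern.** Section 2.4 ties its relaxed α to the question of whether a larger trial is warranted. A reader will look for the place where a result is judged at that α and will not find one in the article. The criterion that does bear on progression uses a different statistic, the sign of a point estimate. The only comparator named for it is control, whereas the effect size came from concurrent versus physical training.

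At stake is the rationale for the follow-on trial. The case for a combined intervention is that it beats its components. As written, the benefit row can be satisfied by concurrent training doing no worse than no training. The estimates that bear on the combination's added value would be available, but no criterion requires anyone to read them.

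**Working it through.** **1. Trace α = 0.25 and the contrasts through the article.**

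| Place | α or interval | Statistic | Comparator |
|---|---|---|---|
| 2.4 Sample size | α = 0.25, 80% power | not stated; called a four-arm calculation | d taken from concurrent vs physical |
| Table 1, Benefit likelihood | none | sign of effect size across most outcomes | none named |
| 2.6.7 Cognitive function | none | consistent negative signs | control, for harm only |
| 2.7 Statistical analysis | none | mixed model, pairwise Cohen's d | all pairs of conditions |
| Hypothesis 2 | none | – | each single modality and wait-list |

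The contrast with physical training is therefore estimated (2.7) and hypothesised (Background), but appears in no progression criterion. The α appears only in 2.4.

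**2. Try to reproduce the plan's sample size.** Inputs from 2.4: d = 0.24, α = 0.25, power 0.80.

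Two-group comparison, n per arm = 2(z_α + z_β)²/d², with z_β = 0.8416:
- one-sided, z = 0.6745: 2 × (1.5161)²/0.0576 = 79.8, so 80 per arm (320 over four arms);
- two-sided, z = 1.1503: 2 × (1.9920)²/0.0576 = 137.8, so 138 per arm (552 over four arms).

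One-way four-group ANOVA needs 402 in total with f = d/2 = 0.12, or 102 if 0.24 is entered as f. A total of about 77 arises only with settings the article does not give. One example is the between-groups effect of a repeated-measures ANOVA with 0.24 entered as f, two measures and correlation 0.5 (first N at or above 80% is 78; power at 77 is 80.0% to one decimal). Another is a group-by-time interaction with f = 0.12, two measures and a correlation near 0.63. Both are omnibus four-group tests. Neither is the concurrent-versus-physical contrast or the sign rule.

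**3. Power of concurrent versus physical at 19 per arm.** SE of d = √(2/19) = 0.3244; d/SE = 0.24/0.3244 = 0.740.
- One-sided: Φ(0.740 − 0.6745) = Φ(0.065) = 52.6% (52.5% by the noncentral t).
- Two-sided: Φ(0.740 − 1.1503) = 34.1% in the favourable tail, plus Φ(−1.1503 − 0.740) = 2.9% in the other, giving 37.0% (36.8% by the noncentral t).

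The effect detectable with 80% power is 1.5161 × 0.3244 = 0.49 one-sided, or 1.9920 × 0.3244 = 0.65 two-sided. A 75% two-sided interval has half-width 1.1503 × 0.3244 = 0.37.

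These figures assume an unadjusted comparison and no dropout. Using the factor (1 − ρ²) for baseline adjustment, 80% at 19 per arm would need ρ = √(1 − 19/79.8) = 0.87 one-sided, or √(1 − 19/137.8) = 0.93 two-sided. The article gives no such correlation.

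**4. How the sign rule behaves (illustration only).** Assumptions: concurrent versus control, 19 per arm, 6 or 7 cognitive outcomes (five computer tasks and the pegboard, with or without FACT-Cog), equal correlation 0 to 0.5, most meaning more than half, positive meaning d > 0. With no true effect the row reads go in 34–43% of trials (6 outcomes) or 50% (7 outcomes). If concurrent is truly +0.24 against control but cycling alone is +0.48, so that concurrent is 0.24 worse than cycling, it reads go in 78–86% (6) or 83–95% (7). These are not error rates to be set against 25%, for the reason given under objection.

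**The case against.** The strongest reply is that the benefit row was never meant to be a signal test. The Abstract lists the principle of no cognitive harm among the feasibility assessments, and Table 1 lets neutral results proceed. Under no effect, go is the intended reading. This stands: a reader might infer that a go rate of 34–50% under no effect is an inflated false-positive rate against a nominal 25%, and the documents do not support that.

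Four further points also stand.
- Section 2.7 already plans pairwise effect sizes, so it would be wrong to say that no analysis addresses concurrent versus physical.
- Section 2.4 takes its d from that pair but never expressly names it as the powered contrast; an omnibus test may have been intended.
- The caution in 2.7 might be read as contradicting 80% power. It is a general remark about pilot studies, names no α, and agrees with the exploratory label in 2.4. It is not a contradiction.
- The row is one of five criteria read together, the primary outcomes are feasibility measures, and the Table 1 row itself names no comparator; control comes from 2.6.7 and only for harm.

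It can also be said that a test level may sit in an analysis plan not shown. That is possible, but it would not change the progression rule this article fixes, nor bring the hypothesis 2 contrasts into it.

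**Conclusion.** The point holds in a limited form. The α and power in 2.4, offered as support for finding signals that inform progression, are not properties of the rule by which cognitive benefit enters that decision. The comparisons that would justify combining the two modalities are planned as estimates but read by no criterion. If 80% is taken to refer to concurrent versus physical, it does not follow from the printed inputs: about 37% two-sided or 53% one-sided at 19 per arm, assuming an unadjusted comparison, no dropout and d = 0.24.

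This is worth correcting but does not undermine the pilot. Its primary aim is feasibility, findings are labelled exploratory, and the overall decision is holistic. The simulated go rates depend on the assumed number of outcomes, their correlation and the meaning given to neutral, and carry no weight beyond illustration.

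**What to change.** 1. **Section 2.7.** Report the pairwise effects already planned (concurrent minus physical, minus cognitive, minus wait-list) for each cognitive outcome with intervals matching the sizing α, that is 75% if two-sided. Define a preliminary signal by those intervals. The general caution about testing can stay.

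2. **Table 1, Benefit likelihood.** Keep the no-harm reading and name wait-list as its comparator. Add that the estimates and intervals for concurrent versus each single modality are also read before progressing with the combined intervention. If most clearly favour a single modality, the row falls in the middle column (possible progression with revisions).

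3. **Section 2.4.** Name the test, contrast and sidedness that α = 0.25 refers to, and restate the power which that contrast has at 19 per arm. Do not assign 80% to concurrent versus physical. Say that these figures are not error rates of the Table 1 criterion.

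The cost is wording in three places and a few intervals from models already planned, with no added participants or assessments. The small downside is that the benefit row becomes somewhat harder to pass.

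### Section 2.4: 19 per arm does not give the stated 80% power for d = 0.24 at α = 0.25 (unadjusted pairwise power is about 37% two-sided, 53% one-sided), and the total is given as both 77 and 76

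*Protocol article*

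**What the plan says.** The protocol article, section 2.4 (Sample size and power calculation), reports that "we have undertaken a modified power analysis utilizing an adjusted alpha (*α* = 0.25"), aimed at picking up preliminary effect signals. The planning effect is drawn from a meta-analysis "comparing concurrent training to physical training in older adults". The section adds that "This power analysis was based on a four-arm study", "with an effect size of *d* = 0.24, 80% power with *α* = 0.25". The resulting size is worded as "we propose to recruit 77 participants, which will result in 19 per intervention arm", with equal allocation.

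The section does not state the test, the sidedness, the number of measurements or the pre-post correlation behind the calculation.

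The total differs elsewhere. The abstract has "Seventy-six men diagnosed with prostate cancer receiving androgen deprivation therapy will be the recruitment target", and section 2.2 (Participants) has "The recruitment target is 76 men with prostate cancer over an ~18-month period". Section 2.2 also equates the target with 19.5% of about 390 expected cases.

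**The concern.** The effect is labelled d and comes from a comparison of two kinds of training, so it reads as a standardised difference between two arms. A difference of about a quarter of a standard deviation is small. Even at α = 0.25, 19 per arm looks far too few to detect it with 80% power.

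Two things are at stake. Section 2.4 rests the sample size partly on the ability to pick up effect signals, and section 2.6.2 says that the pilot will inform power and effect estimates for a larger trial. A reader who trusts the 80% would take the lack of a signal as more informative than it is. The two totals also leave the top recruitment criterion in Table 1, which refers to the designated sample size, without a single value.

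**Working it through.** **Inputs.** From section 2.4: d = 0.24, α = 0.25, target power 80%, four arms, 19 per arm. SD is set to 1, so differences are in SD units. One- and two-sided tests are both shown. Correlations below are assumptions.

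**1. Pairwise, unadjusted, n = 19 per arm (exact noncentral t).**
- Noncentrality = d × √(n/2) = 0.24 × √9.5 = 0.740, with 2 × 19 − 2 = 36 df.
- Two-sided: critical value t(0.875; 36) = 1.169; power = 36.8%.
- One-sided: critical value t(0.75; 36) = 0.681; power = 52.5%.
- Using the pooled error of all four arms (72 df) gives 36.9% and 52.6%.

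**2. Size needed for 80%.** n per arm = 2(z_α + 0.842)²/d², with d² = 0.0576.
- Two-sided: 2 × (1.150 + 0.842)²/0.0576 = 137.8, so 138 per arm (552 in four arms).
- One-sided: 2 × (0.674 + 0.842)²/0.0576 = 79.8, so 80 per arm (320 in four arms).
- With 19 per arm, the d detectable with 80% power is about 0.65 two-sided or 0.49 one-sided.

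**3. Four-arm one-way ANOVA, N = 76 (noncentral F, 3 and 72 df, noncentrality f²N).**
- f = d/2 = 0.12 (two arms on each side, 0.24 apart): 0.0144 × 76 = 1.09; power 39%; N = 402 needed for 80%.
- If 0.24 were itself f: 0.0576 × 76 = 4.38; power 71%; N = 102 needed.

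**4. Pairwise with baseline adjustment.** Adjustment replaces d by d/√(1 − ρ²), where ρ is the pre-post correlation.

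| Assumed ρ | Two-sided | One-sided |
|---|---|---|
| 0.5 | 40% | 57% |
| 0.7 | 47% | 64% |
| 0.8 | 54% | 71% |

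Power of 80% needs ρ of about 0.93 two-sided or 0.87 one-sided. A change-score analysis, with d/√(2(1 − ρ)), needs about 0.93 or 0.88.

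**5. Group-by-time interaction, four arms, two measurements.** Here f = 0.12 reaches 80% at N = 76 with ρ of about 0.63, which looks like a rescue. But with two measurements, and two arms on each side, interaction f is the difference in change divided by 4. So f = 0.12 is a difference in change of 4 × 0.12 = 0.48 SD, twice the stated effect. A difference of 0.24 SD is f = 0.06. Power at ρ = 0.63 is then 44%, and 80% needs ρ of about 0.91.

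**6. Where 77 might come from.** In a four-group repeated-measures test of the between-group factor, the noncentrality is f²Nm/(1 + (m − 1)ρ). With f = 0.24, m = 2, ρ = 0.5 and N = 77 it is 0.0576 × 77 × 2/1.5 = 5.91, and power is 79.999%. The same test with f = 0.12 needs N = 302. Other settings also land nearby: m = 3 and ρ = 0.6 give 80.3% at N = 76. The match is suggestive but does not identify the calculation.

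**7. The total.** 4 × 19 = 76, while 77/4 = 19.25. Also 76/390 = 19.5%, as section 2.2 states, while 77/390 = 19.7%.

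**8. Precision with 19 per arm, unadjusted pairwise.** Half-width = t × √(2/19) = t × 0.324. For 95%: 2.028 × 0.324 = 0.66 SD. For 75%: 1.169 × 0.324 = 0.38 SD.

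**The case against.** The strongest reply is that nothing in this pilot depends on the power figure. Section 2.6.1 makes feasibility measures primary. The benefit-likelihood row of Table 1 goes by the direction of effect sizes across most cognitive outcomes, and neutral results pass. Section 2.4 calls the findings exploratory, and section 2.7 already says that significance is unlikely in small samples and that tests call for caution. This stands. A reader might infer that missed signals would stop a useful programme, but the documents give no route for that.

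Second, the 37% and 53% belong to an unadjusted comparison at one time point, whereas section 2.7 plans linear mixed models on repeated measures. This stands in part. The planned analysis could do better, so the figures must be labelled unadjusted. It does not restore 80% for a pairwise d of 0.24 without a very high correlation that is not stated.

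Third, it would be easy to say that a true d of 0.24 would be missed about two times in three. That is the unadjusted two-sided figure (63%). One-sided it is about 47%, and the article does not give the sidedness.

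Fourth, a reader might conclude that 0.24 was entered as Cohen's f by mistake. The near-exact match at 77 makes this a possible origin, but it rests on a test, a number of measurements and a correlation that the article does not give.

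Finally, 76 against 77 is one participant, and falling one short leads only to the middle column of Table 1 (possible progression with revisions). That is so, but a criterion set at 100% still needs one value.

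**Conclusion.** The power statement is wrong as written. For the comparison that d = 0.24 comes from, 19 per arm gives about 37% power two-sided or 53% one-sided without adjustment. An assumed pre-post correlation of 0.7 raises this to about 47% or 64%. A four-arm one-way ANOVA gives about 39% at f = 0.12. None of the standard readings tried gives 80% from the stated inputs. The conclusion assumes that 0.24 is a standardised two-arm difference, as its label and source indicate. It does not depend on how 77 arose.

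The conflict between 77 and 76 is a plain inconsistency. Equal allocation, the abstract, section 2.2 and the 19.5% figure all point to 76.

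The consequence is a misreported power and a recruitment criterion shifted by one participant. The size of the pilot, its feasibility aims and its progression rules are not undermined. Severity: should be fixed.

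**What to change.** - Use 76 as the total throughout, including section 2.4 and the reference value for the recruitment row of Table 1.
- Withdraw the claim of 80% power for d = 0.24. Alternatively, restate it with the test, the sidedness, the effect metric (d or f), the number of measurements and the assumed correlation, so that it can be reproduced.
- Report what 19 per arm gives, labelled as an unadjusted pairwise comparison at α = 0.25: power of about 37% two-sided or 53% one-sided for d = 0.24; detectable d at 80% power of about 0.65 or 0.49; confidence-interval half-widths of about ±0.66 SD (95%) and ±0.38 SD (75%).
- Justify 76 on feasibility and on the precision of the estimates.

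The cost is a reworded section 2.4 and one corrected number. The stated power becomes less favourable. No extra patients and no change of design or analysis are needed.
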